# Connecting Health and Technology (CHAT): protocol of a randomized controlled trial to improve nutrition behaviours using mobile devices and tailored text messaging in young adults

**DOI:** 10.1186/1471-2458-12-477

**Published:** 2012-06-22

**Keywords:** Nutrition, Diet, Text messaging, Mobile phone, Randomised controlled trial, Tailoring

## Abstract

**Background:**

Increasing intakes of fruits and vegetables intake, in tandem with reducing consumption of energy-dense and nutrient poor foods and beverages are dietary priorities to prevent chronic disease. Although most adults do not eat enough fruit and vegetables, teenagers and young adults tend to have the lowest intakes. Young adults typically consume a diet which is inconsistent with the dietary recommendations. Yet little is known about the best approaches to improve dietary intakes and behaviours among this group. This randomised controlled trial aims to evaluate the effectiveness of using a mobile device to assess dietary intake, provide tailored dietary feedback and text messages to motivate changes in fruit, vegetable and junk food consumption among young adults.

**Methods/design:**

The CHAT project will involve the development of the mobile device food record (MDFR), and evaluation of dietary feedback and implementation of a 6-month intervention in young adults aged 18 to 30 years. The participants will be randomly assigned to one of three groups (1) Intervention Group 1: MDFR + Text Messages + Dietary Feedback; (2) Intervention Group 2: MDFR + Dietary Feedback; (3) Control Group 3: MDFR, no feedback. All groups will undertake a 3-day dietary record using the MDFR but only the Intervention Groups 1 and 2 will receive tailored dietary feedback at baseline and at 6-months which will consist of assessment of serves of fruits, vegetables and junk food in comparison to dietary recommendations. Tailored nutrition text messages will be sent to Intervention Group 1 over the 6 months. Data will be collected at baseline and again at the 6-month completion.

**Discussion:**

This trial will test if applications running on mobile devices have potential to assess diet, provide tailored feedback and nutrition messages as an effective way of improving fruit and vegetable consumption and reducing energy-dense nutrient poor foods in young adults. The CHAT project will assess the impact of the intervention on behavioural intention to eat a more healthful diet. This innovative approach if successful may provide a means to deliver a low cost health promotion program that has the potential to reach large groups, particularly young adults.

**Trial registration:**

Australian and New Zealand Clinical Trials Registry ACTRN12612000250831

## Background

Studies have linked poor diet quality and lack of variety with increased incidence of chronic diseases such as cardiovascular disease, some cancers and diabetes. Increasing fruit and vegetable consumption and limiting energy intake from total fats and sugars are dietary priorities to prevent chronic disease [1]. Inadequate consumption of fruit and vegetables is a major risk factor contributing to 1.8% of the worldwide burden of disease, with Australian estimates at 2.7% [2]. In the US the majority of the population consumes a diet low in fruits, vegetables and whole grains but over-consumes solid fats, sugars and alcoholic beverages [3]. The Australian National Nutrition Survey found that only 8% of Australian adults met the minimum 400 grams of fruit and vegetables recommended by WHO [4]. Only 24-30% of adults met the vegetable target of five or more 75 gram servings per day, compared to 30-37% meeting the recommended two 150 gram servings of fruit per day [5]. Adolescents and young adults were the sub-population group with the lowest fruit intake, while for vegetables about half of all adults were eating less than the recommended serves [6]. Australian adults consume 36 percent of their energy intake from energy-dense nutrient-poor (EDNP) foods and young men typically consume a higher proportion of these foods [7]. Excessive consumption of alcoholic beverages and binge drinking is also common amongst young Australians [8]. Despite the evidence that in Australia young adults consume a diet inconsistent with the dietary recommendations, little is known about the best approaches to improve their dietary intakes and behaviours.

Studies show that adults have an understanding of the relative healthfulness of foods. In Australia, people are comfortable with the term ‘junk food’ when describing foods and drinks of limited nutritional value. ‘Junk food’ or EDNP foods have been defined as any food (including beverages) high in fat, sugar and/or salt with little nutritional value or discretionary/non-core foods such as fast foods, sweetened breakfast cereals, confectionery or fizzy drinks [9,10]. The Australian Guide to Healthy Eating defines non-core foods as ‘extras’ or ‘discretionary’ and specifies the types of foods based on a 600 kiloJoules equivalent [11]. Before adults can improve the quality of their diet they need to have a greater awareness of the recommended number of servings of fruit and vegetables, as well as what constitutes EDNP foods [12,13]. However, many adults are unaware of what they are eating and think their diet is healthy when it isn’t [14,15]. Assessment of food intake in relation to dietary recommendations is necessary so that they are better informed on what constitutes a healthy diet consistent with dietary guidelines.

Assessment of food intake is a difficult task as it requires individuals to verbally describe or orally report in detail the food or beverage consumed and the amount they have had. The traditional dietary record requires individuals to keep detailed written accounts for 3–7 days of all food or drink eaten, including the portion consumed; either estimated in household measures (e.g. cups and spoons) or weighed with food scales. Food records require literate and highly motivated individuals. As this limits those willing to participate, a high degree of bias can occur. Adolescents and young adults, who typically have unstructured eating habits and frequently snack, are the least likely to undertake food records [16]. Obtaining a true picture of what a person eats is challenging. Using a mobile device to capture food intake has great potential to improve accuracy and reduce participant burden [16]. Currently the TADA project has been developing a Mobile Phone Food Record to assess dietary intake [17,18]. The mobile phone application uses a camera to capture before and after images of food and beverages consumed. These images are automatically uploaded to a server for analysis using a Wi-Fi connection. When taking the image, participants need to include a fiducial marker, which acts as a reference of known dimension and markings. The images are automatically analysed for characteristic features in food, such as colour, texture, and intensity, which are then used to identify a food. Together the information from image analysis and volume estimation can be linked to a nutrient database to estimate energy and nutrients consumed. The TADA system is currently being trialled in free-living populations but the full application with automatic image analysis is not yet available for public distribution. The CHAT application described in this paper has been adapted for use on a low-cost mobile device (iPod touch) so that the food images recorded by the participant are automatically uploaded to a server and the assessment of the images is undertaken by trained analysts. The automatic uploading of data will alleviate some of the burden to both participants and researchers. This project will use a food group based approach to provide tailored feedback to participants on their food intake in comparison to dietary recommendations. The over-optimistic perception of current fruit and vegetable intake finds many people believing that they already meet these dietary guidelines and not seeing the relevance of messages to eat more [12]. Providing accurate feedback on their current intake is important. Dietary assessment tools can be used to provide personalised descriptive feedback which can stimulate self-reflection on their eating behaviours [19]. This can assist people in making decisions about the need ‘or not’ to increase or decrease consumption.

Research on promoting dietary change has identified several factors known to be important. These are self-assessment of intake, tailored feedback and goals based on the diet assessment and reinforcement of behaviours with on-going key messages. People want messages which are personally relevant to them. Tailoring or personalising nutrition education messages has been shown to be effective in promoting dietary change [20-22]. Message-tailoring uses characteristics unique to the person to provide a message intended for that person rather than a group with the intention of improving behavioural outcomes [23]. Targeting or market segmentation of messages can be used to direct messages at a group level to reach subpopulations with certain unique characteristics [19]. In developing interventions it’s important to identify which approaches will be used in order to tease out which strategies are effective [23].

Developing the content of nutrition messages to assist people to understand and accept the importance of healthy eating is complex. Nutrition messages should be constructed to raise awareness of key health messages, increase motivation to perform the health behaviour and be relevant to the individual [24,25]. Personal experience and specific eating contexts should be incorporated to increase salience, for example, ‘packable’ or ‘quick and easy’ food [26]. Messages encouraging both individual and social responsibility are effective at increasing consumption [27,28]. The framing of messages is also important. Gain-framed messages which promote the benefits of engaging in a particular behavior are generally thought to be more effective than loss-framed messages for interventions focused on prevention [29]. The ultimate goal is to deliver messages which are persuasive and will lead to behavior change [30]. The additional challenges of delivery messages to a mobile phone is getting the correct content, frequency and length of message and sending at a time when the participant will be most receptive to receiving it.

The CHAT project aims to address the gaps in the existing literature by combining a dietary assessment tool in combination with nutrition messages sent to a mobile phone to support behaviour change. To our knowledge, there are no reported interventions where a mobile device in combination with a mobile phone has been used to measure food intake, provide tailored dietary feedback and support dietary behaviours through tailored nutrition messages. A small number of studies have used mobile phones to deliver health text messages in diabetes [31,32], weight loss [33,34] and smoking cessation [35] and promoting physical activity [36]. Tufano [37] in a review of eHealth (web and mobile phones) interventions for obesity pointed out that for health promotion interventions to be successful in promoting behaviour change they must reach the public. Mobile phones have the potential for a cost-effective and rapid communication of tailored nutrition messages. However, it’s critical that messages are carefully developed and the intervention is based on theoretical constructs. The CHAT project will provide participants with tailored feedback on their dietary intake in combination with tailored nutrition messages segmented by age, gender and behavioural characteristics and suitable for delivery via a text message. The purpose of the CHAT project is to develop a mobile device food record to assess serves of fruits, vegetables and junk (energy-dense nutrient-poor) foods and provide tailored feedback delivered in a timely manner to promote behaviour change in young adults. Additional on-going tailored messages will be delivered to the participants’ mobile phone to assist in the adoption of healthy eating behaviours. This paper describes the protocol of a randomised controlled trial to evaluate the effectiveness of using a mobile device to collect food intake data, provide tailored dietary feedback and tailored nutrition messages about fruit, vegetable and junk food delivered via a mobile phone to promote dietary change among young adults aged 18 to 30 years.

## Methods/Design

### Study design

This project will consist of the development, implementation and evaluation of a 6-month nutrition intervention in young adults aged 18–30 years in metropolitan Perth, Western Australia. The study will be a 6-month randomised controlled trial (RCT) (Figure 1). The program has been designed to increase the intake of fruits and vegetables and decrease the intake of junk food through the use of dietary feedback and on-going motivational messages sent to the participant’s mobile phone. Figure 2 shows the system architecture for the study design. Data will be collected from participants at baseline and at the 6-month completion.

**Figure 1 F1:**
[figure not shown]
CHAT study design.

**Figure 2 F2:**
[figure not shown]
System architecture for the CHAT study Mobile Device Food Record (MDFR).

This intervention will use a mobile device to collect food intake data using an investigator-designed application running on an iPod touch. Each participant will be provided with a study iPod touch. The 3-day mobile device food record will be completed by all participants at baseline and at six months completion. Participants will take images of all food and drinks consumed over a continuous 3 day period. Intervention groups 1 and 2 will receive tailored dietary feedback on the number of serves of fruits, vegetables and junk foods consumed compared with recommended serves by a text message sent to their mobile phone. Intervention group 1 will also receive additional targeted nutrition messages via their mobile telephone (motivational messages on fruits, vegetables and extra foods or recipes) to promote dietary change. Feedback from focus group work indicates that participants recognise the term ‘junk food’ so this term will be used in communications with participants. The project protocol has been approved by the Curtin University Human Research Ethics Committee (approval number HR181/2011) and the Department of Health, Western Australia Human Research Ethics Committee (#2011/90).

#### Sample size

A sample size of 220 is required to estimate the proportion of subjects who will increase their fruit and vegetable intake to within a 95% confidence interval of +/− 7%. Allowing for a drop-out rate of 35%, 100 subjects will be recruited into each of the three treatment group. The sample size calculated for fruit and vegetable serves is based on the results of our pilot study and are conservative since the variability of the data (Standard Deviation) observed was about 4 times that reported in other studies.

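### The sample-size figures do not agree: 300 recruits with 35% drop-out leave 195 completers, not the 220 stated as required

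*Protocol article*

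**What the plan says.** The Sample size section of the protocol article holds the only sample-size justification in the document. It gives four figures:

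- a required number: "A sample size of 220 is required to estimate the proportion of subjects who will increase their fruit and vegetable intake";
- a precision target in percentage points: "to within a 95% confidence interval of +/− 7";
- an attrition allowance and a recruitment target, in one sentence: "Allowing for a drop-out rate of 35%, 100 subjects will be recruited into each of the three treatment group".

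No expected proportion is given and no formula is shown for either step. No other section gives a different recruitment total or drop-out rate. On timing, the Study design section says: "Data will be collected from participants at baseline and at the 6-month completion".

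**The concern.** The paragraph reads as a short chain: a required number, a loss rate, and a recruitment target that allows for the loss. Carried through, the chain should return to the required number, and it does not. A reader would take the trial to expect 220 analysable participants, about 73 per group. At its own planned attrition it expects 195, or 65 per group. Any later judgement of whether the trial reached its planned size depends on which of the two is the target.

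**Working it through.** **Inputs, all from the Sample size section:** required number 220 in total; drop-out 35%; recruitment 3 × 100 = 300; 95% half-width 7 percentage points. **Assumption:** the expected proportion is not stated, so p = 0.5 is used as the worst case, with one lower value for range.

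**1. Reproducing the plan's 300.**
- Multiplying by one plus the loss rate: 220 × 1.35 = 297, or 99 per group, which rounds to 100.
- Dividing by the retained fraction: 220 / 0.65 = 338.5, so 339, or 113 per group.

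Of these two, only the multiplication leads from the printed 220 to the printed 300.

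**2. Completers under the stated design.**
- 300 × (1 − 0.35) = 195, or 65 per group.
- Shortfall: 220 − 195 = 25, and 25 / 220 = 11%.
- Highest loss at which 300 recruits leave 220: 1 − 220/300 = 26.7%.
- Check on division: 339 × 0.65 = 220.4.

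**3. Precision, with half-width = 1.96 × √(p(1 − p)/n).**

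| Completers | p = 0.5 | p = 0.3 |
|---|---|---|
| 195 | 7.02 points | 6.43 points |
| 220 | 6.61 points | 6.06 points |

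The largest difference is about 0.4 points. With other intervals at 195 completers and a proportion of about 0.5, the half-width is 6.95 points (Wilson) and 7.23 points (exact binomial).

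**4. Where 220 might come from.** The simple formula for 7 points at p = 0.5 gives 1.96² × 0.25 / 0.07² = 196, or about 210 with a continuity correction. Neither is 220, but 220 exceeds both and so satisfies the target. Also, 196 / 0.65 = 302, close to 300. A correct inflation of 196 would therefore explain the recruitment figure as well, and 220 would then be the misstated number.

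**5. Other readings of the paragraph.**
- *220 per group:* not possible with 100 recruited per group.
- *220 already includes the allowance:* recruitment would then be 220, not 300.
- *The 35% is lost before randomisation:* the 100 are counted into each treatment group, and the Recruitment section randomises only after the baseline food record. The loss therefore falls on the 300.
- *Drop-outs still count towards 220:* the quantity to be estimated is the proportion who increase their intake, which needs a six-month measurement.

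None of these reconciles the figures.

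**The case against.** The strongest reply is that nothing of substance is lost. The only performance figure in the paragraph is a half-width of 7 points, and 195 completers give 7.02 in the worst case and less at any other proportion. The article states no power figure. The main analysis in the Outcome variables section is an analysis of covariance of change in serves between three groups, and a pooled one-proportion calculation does not fix the precision of those comparisons. This stands, and it limits the consequence. It does not reconcile 220, 35% and 300.

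Three stronger readings are tempting, and the document does not support them.

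- *The allowance was multiplied where it should have been divided.* The multiplication fits the printed figures, but no formula is shown, and a correct inflation of 196 fits 300 about as well.
- *220 contradicts the 7-point target.* It gives 6.6 points at p = 0.5 and so meets it. Exceeding a minimum is not an error, and a condensed article need not show its pilot inputs.
- *The trial's precision or power is materially overstated.* No power is claimed, and the stated precision is essentially kept.

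**Conclusion.** The paragraph is wrong as written. The required number of 220, the 35% drop-out and the 3 × 100 recruits cannot all be correct. At the stated loss the design yields 195 completers, 25 (11%) short, and it reaches 220 only if loss is at most 26.7%. This is arithmetic on the printed figures and needs no assumption beyond reading 220 as completers, which the quantity being estimated requires.

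The practical effect is small. Assuming p = 0.5 and the usual normal approximation, the pooled half-width moves from 6.6 to 7.0 points; an exact interval at 195 is slightly wider, at 7.2. Which figure is mistaken cannot be settled from the document. What needs correcting is the sample-size statement; the finding gives no reason to change the size of the trial.

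**What to change.** Keep 100 per group and restate the paragraph so that its figures agree: 300 randomised; 195 expected completers (65 per group) at 35% loss; pooled 95% half-width of about ±7.0 percentage points at p = 0.5, with the assumed proportion stated. Then either remove the statement that 220 are required, or say that 220 completers corresponds to about 27% loss.

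The cost is a wording correction to one paragraph. It needs no extra participants and changes no arm, endpoint or analysis. The stated completer number becomes less favourable by 25 and the worst-case precision by about 0.4 points.

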### Recruitment

Participants from 57 suburbs (neighbourhoods) within in the Perth metropolitan area will be selected from the electoral roll in Western Australia. Suburbs will be selected to provide representation across socio-economic status (SES) based on the Socio-Economic Index for Area (SEIFA) [38] a value derived from income, education level, employment status and skill level. Using the Federal Electoral Roll, the first sample will contain 5000 names and addresses. A second sample will be used if required and will contain the same number or less, depending on the recruitment rate after the first mail out. The research team will not have access to the names and address data. These data will be delivered to a company approved by the Department of Health to conduct the mail out. After receiving a letter of invitation, participants who wish to take part in the study will contact the research team by email, mobile phone or the study website. Participants need to be aged between 18 to 30 years as of their last birthday and have a mobile phone. Participants will be excluded if (a) pregnant; (b) unable to complete the 6 month study; (c) undertake extreme forms of exercise or dieting; or (d) unable to attend the study centre on four occasions (two at baseline and two at completion).

Participants will undergo a telephone or on-line screening questionnaire. If they meet the selection criteria, once being informed of the details of the study and if willing to participate, they will be asked to attend a baseline data collection session at Curtin University which will include training on the use of the mobile device food record (MDFR). The study objectives and requirements will be explained to the participants who will complete an informed consent and have their height and weight recorded by the research staff. They will also complete a demographic and personal characteristics questionnaire. They will undertake the MDFR for three consecutive days (Thursday-Saturday). The following week, participants will return the mobile device and will then be randomized to one of three treatment groups. Sequence generation will be conducted by a biostatistician not involved in the implementation of the trial on site (therefore not in contact with the study participants). Research staff will not be involved in the randomisation or have access the randomisation sequence. Participants will be randomised to one of three treatment groups using a randomisation table created by computer software: (1) Intervention Group 1: MDFR + Text Messages + Dietary Feedback; (2) Intervention Group 2: MDFR + Dietary Feedback; (3) Control Group 3: MDFR, no feedback. Study participants or research staff cannot be blinded to the intervention. Research staff will need to liaise with the participants throughout the study.

Participants will complete additional questionnaires on their dietary habits and useability of the MDFR. Six months later they will be asked to repeat the 3-day MDFR and evaluation questionnaires. All three groups will record their food intake using the MDFR. The intervention groups will receive feedback on their food intake for serves of fruits, vegetables, junk food and alcohol. Participants will be forwarded dietary feedback and messages to their own mobile phones. Intervention Group 1 will receive additional weekly text messages on nutrition throughout the six months of the study. The control group will undertake the MDFR but will not receive feedback or text messages.

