### Training on use of the mobile device food record

The MDFR has been developed by the research team at Purdue University [17,43]. The MDFR application was adapted for use in CHAT and allows for the automatic uploaded of food images collected by participants. When taking an image, participants need to include a scaling device known as a fiducial marker.

The training session on the use of the MDFR will take place at Curtin University in a room which has Wi-Fi access. All participants will be asked to keep a 3-day food record (1 weekend, 2 week days) with the special food recording application developed for a mobile device (iPod touch). Participants will undergo a briefing session on how to use the MDFR which will be used to record meals, drinks or snacks for a 3-day period.

The training session will be interactive and consist of a presentation using a 3D animated character which will include instruction on how to use the application (e.g. how to check if connected to Wi-Fi, how to capture food images). Previous research has shown that making the training session fun and interesting can improve cooperation and interest [17]. The animated character will be developed by a member of the project team (KK) who is multimedia designer and a 3D animator. The training will also include a practical session where participants will practice taking an image of a meal and successfully sending the image to the server. Participants will have a small booklet, designed to fit into the iPod carry case, for recording foods they forget to capture via the mobile device along with written and pictorial instructions on how to use the MDFR. All participants will receive a text message to remind them to start recording on the morning of the first day of their intervention and a second reminder in the evening to prompt them for any forgotten food. The following week, participants will return the mobile device and the research staff will verify the content of the images with participants (this is the normal procedure for paper-based food records). They will complete a questionnaire on the useability of the MDFR to guide the research team in future developments of the MDFR.

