### Dietary feedback

The Intervention groups 1 and 2 will receive tailored feedback based on an assessment of their food intake from their MDFR. The participant’s 3-day diet will be assessed using a quality scoring of food items using food group analysis which will include serves and variety of fruits, vegetables and “junk food”, defined as foods and drinks high in fat, sugar and/or salt and alcohol with little nutritional value - or in colloquial food terms, fast foods, sweetened breakfast cereals, confectionery, fizzy drinks or alcohol [9,10]. Serving sizes for dietary assessment and feedback will be based on Australian Guide to Health Eating (AGHE) for fruits and vegetables (one serve of fruit is 150 g and one serve of vegetables is 75 g) and ‘discretionary food or extra serves (equivalents of approximately 600 kilojoules) [11]. Once the scoring is complete, the Intervention groups will be sent a text message with tailored feedback on the number of serves of food groups they consumed averaged over three days of recording, compared to recommended serves for adults from the AGHE. They will be prompted to set specific goals to increase serve of fruits and vegetables and reduce junk foods, where required.

### Nutrition messages to intervention group 1

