### Primary outcome measures

The serves of fruits, vegetables, junk and alcohol foods and beverages are the primary outcomes. Dietary intake will be assessed by the 3-day MDFR and scored for number of serves of fruits, vegetables and discretionary food according to the Australian Guide to Healthy Eating [11] standard serves as outlined previously by Rangan and colleagues [7].

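### The blinding statement covers research staff of every role for a reason that fits only contact staff, so the analysts who score the primary outcome from images are not protected from knowing the arm

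*Protocol article*

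**What the plan says.** On blinding, the Recruitment section states: "Study participants or research staff cannot be blinded to the intervention". The sentence that follows is the only justification: "Research staff will need to liaise with the participants throughout the study". No role within the research staff is set apart. The same section keeps research staff away from the randomisation and its sequence, which is a matter of concealment before assignment.

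On the outcome, the Primary outcome measures section states: "The serves of fruits, vegetables, junk and alcohol foods and beverages are the primary outcomes". It adds: "Dietary intake will be assessed by the 3-day MDFR and scored for number of serves of fruits, vegetables and discretionary food". The Background explains who does this work: the "food images recorded by the participant are automatically uploaded to a server and the assessment of the images is undertaken by trained analysts".

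One step in the outcome chain does need contact. Under Training on use of the mobile device food record, when the device comes back, "the research staff will verify the content of the images with participants".

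**The concern.** Whether masking is feasible depends on what each person does. Someone who trains, weighs or telephones participants over six months will probably learn the arm. Someone who scores photographs held on a server need not. The article applies one statement to both kinds of work and supports it with a reason that fits only the first.

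The scoring involves judgement. The Background says that the full application with automatic image analysis is not yet publicly available and that people assess the images in this trial. They have to convert pictures into serves of 150 g fruit, 75 g vegetables or about 600 kJ of discretionary food (Dietary feedback). An analyst who knows the arm and expects the intervention to work can tilt borderline calls without intending to.

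Such a tilt in six-month scores would pass straight into the between-arm difference in change. Adjustment for baseline, age and gender, as considered under Outcome variables, would not remove it, because none of these covariates records how the six-month images were scored.

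**Working it through.** There is no figure in the plan to reproduce on this point. The check is mainly a comparison of sections, with a short calculation for scale.

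**Sections side by side**

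1. *Reason for not blinding* (Recruitment): contact with participants.
2. *Work that produces the primary outcome* (Background; Primary outcome measures): trained analysts score images that were uploaded automatically. Nothing in that description requires contact.
3. *Does concealment cover it?* No. Withholding the sequence protects assignment. It does not limit who knows the arm afterwards.
4. *Is masking stated anywhere else?* The sections on recruitment, training, dietary feedback, the control group and outcomes do not mention coded images, masked scoring or separation of analysts from contact staff.
5. *Would the images reveal the arm?* All three groups use the same recording tool, so the recording method gives no sign of allocation.
6. *Which time point is exposed?* Randomisation follows return of the device after the baseline record (Recruitment). Baseline images are therefore recorded before allocation, although the article does not say when they are scored. Six-month images are recorded after allocation and enter the change score directly.

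**Illustration of scale**

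Inputs from the article: 100 per arm and 35% drop-out (Sample size), so n = 100 × (1 − 0.35) = 65 completers per arm; significance level 0.05 (Outcome variables). Assumptions: a two-sided test, no true effect, one pairwise comparison, no covariate adjustment, and a differential scoring tilt of b standard deviations of change. The documents give no value for b.

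Standardised shift: s = b / √(2/n), with √(2/65) = 0.1754.

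Rejection probability: 1 − Φ(1.96 − s) + Φ(−1.96 − s).

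| Assumed b (SD) | s | False-positive rate, n = 65 per arm |
|---|---|---|
| 0 | 0 | 5.0% |
| 0.05 | 0.285 | 5.9% |
| 0.1 | 0.570 | 8.8% |
| 0.2 | 1.140 | 20.7% |
| 0.3 | 1.710 | about 40% |

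With all 100 per arm retained, the rates for b = 0.05, 0.1, 0.2 and 0.3 are 6.4%, 10.9%, 29.3% and 56.4%. More participants do not dilute this kind of error. They make it easier to declare significant.

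**The case against.** The strongest reply is that the article never says the analysts belong to the research staff. It uses one term for those who score images and another for those who measure, liaise and verify. If the groups are separate, the blinding sentence may not concern the analysts, and a condensed article may leave assessor masking to the full protocol. Part of this stands: a reader might infer that the analysts are unblinded or will be told the arm, and the text does not support that. The point survives because the article takes a position on blinding, draws no distinction by role, and gives a reason that cannot apply to image scoring.

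A reader might also infer that the order of scoring reveals the arm, since "Once the scoring is complete, the Intervention groups will be sent a text message with tailored feedback" while controls wait for theirs. The documents do not support this. No section says that control images are scored later. At six months the Abstract again gives feedback to both intervention groups, and the Control group section promises controls feedback after the study, so all three arms then need scores.

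Three further replies carry some weight:

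- The scoring has anchors: a marker of known dimensions in each image and fixed serve sizes. This narrows the room for judgement but does not remove it.
- The tilts in the illustration are assumed, and any unmasked measure would give the same table. It shows sensitivity and is not evidence of bias in this trial.
- Participants know their arm and choose what to photograph or note in the booklet, and masked scoring leaves that untouched. It is still no reason to accept a second source of bias that can be avoided.

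On verification, the baseline step appears to come before randomisation. A six-month verification is not described, though it is plausible, since Recruitment requires two visits at completion.

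**Conclusion.** The point holds in a limited form. The blinding statement is broader than its reason, and it leaves the people who generate the primary outcome unprotected from knowing the arm, above all for the six-month images. The article supports saying that analysts can know the arm; it does not show that they do.

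The size of any bias is unknown. The range of about 9% to 40% for one pairwise test rests on assumed tilts of 0.1 to 0.3 SD, 65 completers per arm, no true effect and no covariate adjustment. It should be read as a reason for a cheap safeguard and not as an estimate. The change should be made because the outcome is primary, masking looks feasible with images already on a server, and a scoring tilt cannot be corrected in the analysis.

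**What to change.** Restate the blinding sentence in Recruitment by role: participants and contact staff are unblinded; image analysts are masked to arm. To make that hold in practice:

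- Give analysts the images under coded identifiers, with all three arms mixed in one queue at each time point.
- Have the feedback texts prepared from the completed scores by existing team members other than the analysts.
- If images are verified with participants at six months, use a fixed script and complete it before any feedback is discussed.

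Masking to visit is not requested. Baseline records have to be scored early to produce feedback, and a separate queue for each time point shows the visit anyway.

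The cost is minor file coding on the existing server, a scripted form and some reallocation of tasks. This assumes that the team is large enough to separate scoring from feedback, which the article does not state. Verification by contact staff and self-recording by participants remain unblinded, and the report should say so.
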